#### Clinician recruitment

All PWP clinicians will be invited to a brief information session where the trial and the objectives will be fully described. They will be invited to participate as clinical supporters for the iCBT (*Space from Depression* and *Space from Anxiety*) interventions, but also as research participants themselves. As research participants PWPs will:Electronically sign informed consentComplete STAR-C and therapist behaviours checklist after each review session with a clientParticipate in a semi-structured interview post-trial about their experience of the therapeutic alliance and their use of therapist behaviours.

#### Randomisation and blinding

Based on the outcome from the M.I.N.I., PWP’s will establish a primary diagnosis of depression or anxiety disorder and allocate participants to the depression or anxiety arm, respectively. Participants will be randomised using an algorithm performed by a computer scientist and executed independently of the research team, employing random permuted blocks using block sizes of 9, and including stratification within a 2:1 allocation ratio between the treatment group and the waiting list control group. The PWP who carries out the support and assessment of the patients cannot be blinded to allocation for practical reasons.

Intervention: SilverCloud platform.

SilverCloud Health are global leaders in the development of computerised psychological interventions for depression, anxiety, stress and comorbid long-term conditions. Both treatments, depression and anxiety, are delivered on a Web 2.0 platform using media-rich interactive content. This platform employs several innovative and engaging strategies for improving the user experience. The programme content is delivered in a non-linear fashion.

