#### Client recruitment

Recruitment will begin in June 2017 and will continue for 9 months until the numbers are reached or exceeded. Given that prevalence of anxiety disorders is higher than depression, it might be the case that the numbers on the anxiety arm will be reached before the depression arm. If necessary, recruitment on the anxiety arm will be stopped, but patients with primary diagnosis of a specific anxiety disorder will be still offered treatment.

Regarding the recruitment process, firstly, individuals will be given an initial assessment by phone with a Psychological Wellbeing Practitioner (PWP) clinician at Berkshire IAPT service. The assessment will determine if an individual meets the eligibility criteria, and an initial indication of depression, anxiety, or comorbid depression and anxiety will be advised by the PWP. The PWP will then describe the trial and invite the client to participate. Those interested will be assigned a further telephone appointment, to complete a structured clinical interview, the Mini-International Neuropsychiatric Interview (M.I.N.I.) [37]. They will also receive an email with information detailing the study and a link to give consent by means of a digital signature. Upon giving consent, participants will complete the primary and secondary outcomes for the study online (described below). During the M.I.N.I. appointment, the PWP will reiterate details of the research and the programme, describing what is involved and the importance of their participation in the trial. Participants will be allocated to the depression or anxiety arm based on the outcome of the M.I.N.I., and then randomized to the treatment or the waiting-list group. They will be informed of the outcome of randomisation during this appointment. Participants will then receive an email confirming whether they are in the immediate treatment group or waiting list group, and how to proceed. All participants will be informed they are free to withdraw if they no longer wish to take part in the trial. In this case, they will be removed from the trial and they will be offered treatment as usual.

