### Measures

#### M.I.N.I. International neuropsychiatric interview 7.0 (MINI) [37]

The current version is 7.0 and is based both on the Diagnostic and Statistical Manual of Mental Disorders (DSM-5) and the International Classification of Diseases (ICD-10) criteria. The interview has been well validated and the administration of the interview by telephone has been validated. The Interview schedule will include the following modules: Module A (Major Depressive Episode), Module D (Panic Disorder), Module F (Social Anxiety Disorder), and Module N (Generalized Anxiety Disorder), in order to establish current depression and anxiety and specific anxiety presentations. For research purposes randomisation to either *Space from Depression* or *Space from Anxiety* will be based on the outcome from the M.I.N.I. In the event where a clear diagnosis is not available the clinician will decide on the diagnosis based on the outcome from the M.I.N.I. and clinical knowledge from the initial assessment (scores on the PHQ-9, GAD-7).

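### A single fixed block size of 9 at 2:1 leaves up to 21% of allocations deducible by a fully informed observer; varying the block size would remove most of this cheaply

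*Protocol article*

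**What the plan says.** The Randomisation and blinding section of the protocol article sets out the scheme. On generation and execution: "Participants will be randomised using an algorithm performed by a computer scientist and executed independently of the research team". On the blocks: "employing random permuted blocks using block sizes of 9", "including stratification within a 2:1 allocation ratio between the treatment group and the waiting list control group". The stratification factors are not named, and no variation in block size is mentioned.

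The same section gives PWPs the diagnostic decision: "PWP’s will establish a primary diagnosis of depression or anxiety disorder and allocate participants to the depression or anxiety arm, respectively". It also states: "The PWP who carries out the support and assessment of the patients cannot be blinded to allocation for practical reasons".

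Two other sections bear on this:

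- **Client recruitment.** Eligibility is assessed at an initial phone call. A further appointment covers the M.I.N.I., after which the patient is placed in a diagnostic arm and then randomised. On disclosure to participants: "They will be informed of the outcome of randomisation during this appointment".
- **M.I.N.I. (under Measures).** There is room for judgement: "In the event where a clear diagnosis is not available the clinician will decide on the diagnosis", using the interview result and what is known from the initial assessment.

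**The concern.** With one block size and a 2:1 ratio, each block has a known content. Once three waiting-list or six iCBT places have been used in a block, the remaining places are determined. Independent execution of the algorithm protects the list itself. It does not stop staff inferring the rest of a block from allocations already made.

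The staff who learn allocations also act before randomisation. By setting the primary diagnosis, a PWP decides which list the patient joins, and in unclear cases that is a matter of judgement. Such cases need not be rare: Client recruitment lists comorbid depression and anxiety as an expected presentation, and the Space from Depression section calls comorbidity with anxiety symptoms frequent. A PWP who could foresee the next place on a list might, even unconsciously, time an appointment or settle a borderline diagnosis accordingly.

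The result would be selection bias at entry, which intention-to-treat analysis cannot fully repair. The comparison is also open, against an untreated waiting list, with self-reported symptoms on the PHQ-9.

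**Working it through.** **Inputs**

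- Block size 9, ratio 2:1 (Randomisation and blinding): 9 × 2/3 = 6 iCBT and 9 × 1/3 = 3 waiting list.
- Planned size (Sample size): 144 × 1.25 = 180 per diagnostic arm, as 120 + 60, and 360 in total. This agrees with the article.
- The article states no predictability figure, so there is none to reproduce.

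**Ceiling for a fully informed observer**

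Assume the observer knows the block size and boundaries and has seen every earlier allocation in the list. An allocation is then certain when one group's places in the block are used up.

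- Expected run of iCBT places after the last waiting-list place: 6/(3 + 1) = 1.5 per block, or 1.5/9 = 16.7%.
- Expected run of waiting-list places after the last iCBT place: 3/(6 + 1) = 0.43 per block, or 0.43/9 = 4.8%.
- Total: 1.5 + 0.429 = 1.929 per block, or 1.929/9 = 21.4%.

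Enumerating all 84 orders of a 6:3 block gives the same result by position:

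| Position in block | Probability that it is certain |
|---|---|
| 1 to 3 | 0 |
| 4 | 1.2% |
| 5 | 4.8% |
| 6 | 11.9% |
| 7 | 25% |
| 8 | 50% |
| 9 | 100% |

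These sum to 1.929. If diagnosis is the only stratum, each arm has 180/9 = 20 blocks. The ceiling is then 20 × 1.929 = 38.6 of 180 allocations per arm, or about 77 of 360.

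Counting uncertain guesses too, the best guesser is right 72.8% of the time, against 66.7% for always guessing iCBT.

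**An observer who sees only part of the list**

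Assume a PWP sees a random share of the list but still knows the block boundaries. The share of that PWP's own patients whose allocation is certain, by simulation of 100,000 blocks, is:

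| Share of list seen | Certain |
|---|---|
| 100% | 21.4% |
| 50% | 2.2% |
| 25% | 0.25% |
| 10% | 0.01% |

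**Effect of varying the block size**

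Assume an observer who sees everything and knows the set of possible sizes, but not the current one. Sizes are equally likely and lists have 180 places (simulated).

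| Block sizes | Certain | Best guess right |
|---|---|---|
| 9 only | 21.4% | 72.8% |
| 6, 9, 12 | 2.2% | 71.6% |
| 3, 6, 9 | 3.9% | 73.7% |

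Varying the size removes most of the certainty but only a little of the general guessing advantage. Including blocks of 3 makes that advantage slightly larger than with a fixed block of 9.

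**The case against.** The best case for the plan is that nothing in the article shows anyone can track a list. It does not say that PWPs know the block size, know where blocks begin, or see colleagues' allocations. All PWPs in the service are invited to take part, and the service treats more than 11,000 people a year, so one PWP may see only a small part of each block. Nine is also three times the smallest possible block at 2:1. This argument stands as a limit on size: 21.4% cannot be read as the expected rate.

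Several stronger readings are tempting, and the documents do not support them:

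- **PWPs run the randomisation.** The article says the algorithm is executed independently of the research team. PWPs choose the diagnostic arm and learn the result.
- **A PWP can reject a patient as unsuitable in the appointment where allocation is disclosed.** Eligibility is settled at the preceding phone assessment, and the diagnostic arm is set before randomisation. The routes left are judgement in unclear diagnoses and possible delay.
- **One waiting-list place in five could be foreseen and avoided.** Certain waiting-list places are 4.8% of allocations even at the ceiling. Most of the 21.4% are iCBT places.
- **Stratification pushes the true rate towards the ceiling.** The strata are not named. Splitting a list would have this effect only if strata followed individual PWPs, which the article does not say.
- **The article is at fault for not describing a system lock on eligibility and diagnostic arm.** A condensed article may leave that operational detail to the full protocol.

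The fixed block size does not fall under that last allowance, because the article states it outright.

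**Conclusion.** The point holds as an inexpensive improvement to a stated design rule. It does not show that allocation was or will be subverted. A single block size of 9 at 2:1, with unblinded PWPs who choose which list a patient enters, leaves up to 1.93 of 9 allocations (21.4%) deducible.

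That ceiling requires knowledge of the block size, the boundaries and all earlier allocations in the list. It falls to about 2% for a PWP who sees a random half of the list and becomes negligible at a tenth. Where the trial lies in this range cannot be settled from the article, which gives neither the number of PWPs nor what they see. The count of about 77 of 360 also assumes that diagnosis is the only stratum. The size of any resulting bias in the treatment effect is unknown.

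**What to change.** In Randomisation and blinding, replace the fixed block of 9 with block sizes that vary at random in multiples of 3, for example 6, 9 and 12, and state that the sizes are not disclosed to PWPs. Blocks of 3 are best left out, for the reason shown by the simulation. The Trial status section says recruitment has begun, so the change would apply to the unused part of each list.

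The cost is a small change to the allocation algorithm and one sentence of text. The statistical price is a possible departure from 2:1 of a few participants at the end of a list. The present scheme avoids this only if recruitment stops on a complete block, as it would at exactly 180 = 20 × 9 with one list per diagnostic arm.

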#### Sample size

Sample size was determined separately for primary presentations of anxiety disorders and depression for the trial. Using the software program G-power [36] and based on a moderate between group effect size of *d* = 0.5 with a power of 80%, an alpha error of 0.05, and a 2:1 randomisation procedure into immediate treatment and a corresponding waiting list control group. This calculation returned a total sample of 144 participants in the depression arm (96 in the treatment group and 48 in the WL group) and the same for anxiety, leading to a total of 288 participants. To ameliorate against attrition, a 25% uplift was added, resulting a total sample size of 360. Therefore, this number translates to a ratio of *n* = 120 in the treatment group and a corresponding *n* = 60 in the control group for depression, and the same ratio for anxiety. The 2:1 randomisation procedure was implemented to reduce the likelihood of having many people waiting for treatment after presenting to the IAPT service.

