### Statistical analysis

The effectiveness of the internet-delivered interventions compared to control will be analysed using the intention to treat (ITT) approach. Participation levels will be monitored throughout the study and reasons for withdrawal or non-compliance of study subjects will be recorded to document bias associated with non-random protocol deviations. Any potential imbalances will be reported and considered fully in interpretation of the trial results. Missing data will be evaluated for randomness and imputed using multiple imputation procedures.

Differences in baseline primary and secondary outcome measures between treatment groups and waiting list control groups will be identified using χ^2^ tests for categorical variables and ANOVAs or t-tests for continuous variables. Efficacy of treatments over time will be measured using mixed effects models. To complement the post-hoc comparisons, the magnitude of change within and between the groups on the primary and secondary outcomes measures will be established using Cohen’s *d* statistic. Bonferroni corrected *p*-values will be reported for multiple comparisons. All statistical analyses will be conducted in SPSS, SAS and R. Results will be presented following CONSORT guidelines for reporting parallel group randomised trials.

The established IAPT definitions of recovery will be used in our analysis, where ‘recovery’ is determined by patients moving from ‘caseness’ at the beginning of the intervention (i.e. scoring ≥9 on the PHQ-9 or ≥8 on the GAD-7) to ‘non-caseness’ at the end of treatment (thus scoring below the cut-off). Two further established measures will be considered: *reliable improvement*, where the patient has a significant decrease in their PHQ-9 / GAD-7 score upon completion of their course of treatment; and *reliable recovery*, where the patient meets the criteria for both recovery and reliable improvement. Thus, a patient who moves from caseness to non-caseness, and does so by showing a significant decrease in their symptom scores, is said to have a reliable recovery [44].

Exploratory analyses, including the use of correlation and multiple regression, will be conducted to explore the role that mechanisms of change and maintenance measures play in the benefits obtained from the interventions. Moderation and mediation analyses may include the use of macros for SPSS and/or bootstrapping for exploring the role that mechanisms of change play on the outcomes.

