Resource-use and subsequent costs will be estimated over the 12-month time horizon for the intervention group and for the 8-week waiting list time period for the control group. Healthcare resource will be valued using unit costs derived from available data sources [62–66].

For the purpose of the economic evaluation, EQ-5D-5 L and ReQoL-10 preference-based tariff score values will be used to elicit the quality adjusted life year (QALY) using the area under the curve (AUC) method to account for the collection of this data at multiple time points between baseline and 12-month follow-up in both trial-arms. The proposed economic analysis will be conducted for those with anxiety and those with depression separately and as a whole patient group. All economic analysis will be performed using Stata version 14 (or an updated version). Due to the shorter time horizon of the control groups (8 weeks based on a waiting list approach) compared to the intervention group (12 months with outcome assessment at 8 weeks, 6 months, 9 months and 12 months), methodological work will be carried out to assess the feasibility and uncertainty around extrapolating outcomes from the 8-week time period in the control group to a longer time horizon (e.g. 6-months, 9-months and 12-months) using survival analysis methods [67]. Cost per QALY analysis will be carried out over multiple time horizons (e.g. 8-weeks, 6-months, 9-months and 12-months) to address the uncertainty around decision making from using observed data (up to 8 weeks) and extrapolated outcomes (beyond 8 weeks) for the economic evaluation. Incremental mean point estimates of the difference in cost and QALYs between trial groups will be used to determine the incremental cost effectiveness ratio (ICER). ICER is defined here as the ratio between incremental costs and incremental effectiveness and the following formula will be employed:$$ ICER=\frac{\mathrm{Cost}\kern0.5em \mathrm{active}\kern0.5em \mathrm{intervention}\kern0.5em \mathrm{group}\hbox{-} \mathrm{Cost}\kern0.5em \mathrm{control}\kern0.5em \mathrm{intervention}\kern0.5em \mathrm{group}}{\mathrm{Efectiveness}\kern0.5em \mathrm{or}\kern0.5em \mathrm{Utility}\kern0.5em \mathrm{active}\kern0.5em \mathrm{intervention}\kern0.5em \mathrm{group}\kern0.5em \hbox{-} \mathrm{Efectivenes}\kern0.5em \mathrm{or}\kern0.5em \mathrm{Utility}\kern0.5em \mathrm{control}\kern0.5em \mathrm{intervention}\kern0.5em \mathrm{group}}. $$

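### The whole-group cost-effectiveness analysis pools two separately randomised diagnostic arms with no stated term for diagnosis, so its uncertainty may be modestly overstated

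*Protocol article*

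**What the plan says.** **Allocation.** Under Client recruitment, the diagnostic interview decides the arm and randomisation follows: "Participants will be allocated to the depression or anxiety arm based on the outcome of the M.I.N.I., and then randomized to the treatment or the" waiting list. Randomisation and blinding repeats this order and describes the method as "employing random permuted blocks using block sizes of 9, and including stratification within a 2:1 allocation ratio". No stratification factor is named there. Diagnosis is the only one the article suggests.

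**Sizing.** "Sample size was determined separately for primary presentations of anxiety disorders and depression for the trial". Each diagnosis has 96 + 48 = 144 before attrition and 120 + 60 = 180 after the 25% uplift, so both share the 2:1 ratio and the total is 360.

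**Clinical analysis.** "Efficacy of treatments over time will be measured using mixed effects models". The Statistical analysis section neither lists nor excludes covariates, and does not say whether these models are run by diagnosis.

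**Economic analysis.** "The proposed economic analysis will be conducted for those with anxiety and those with depression separately and as a whole patient group". The estimator is then set out: "Incremental mean point estimates of the difference in cost and QALYs between trial groups will be used to determine the incremental cost effectiveness ratio (ICER"). A formula of active minus control follows. Uncertainty is to be shown by a bootstrapped CEAC. If considerable uncertainty about cost-effectiveness remains, a decision model and an expected value of information analysis are to follow. Diagnosis appears in neither the estimator nor the bootstrap.

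**The concern.** The trial is in effect two separately filled 2:1 lists. Treatment is balanced within each, so a difference in cost or QALY level between depression and anxiety patients cannot leak into the treatment contrast. An analysis gains from that balance only if it conditions on diagnosis.

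A whole-group difference in raw means, with a bootstrap that resamples without regard to diagnosis, counts the spread between diagnoses as random error. The point estimate stays right on average, but its stated uncertainty is too large. Such a difference is plausible: the two arms receive different programmes, and the sponsor already intends to report them separately.

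At stake are the whole-group CEAC and the decision that depends on it. An overstated spread makes the curve flatter and pushes the result towards the condition that starts further modelling.

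**Working it through.** **1. The plan's own figure.** Inputs from Sample size: "moderate between group effect size of *d* = 0.5", "with a power of 80%, an alpha error of 0.05, and a 2:1 randomisation procedure". For a two-sided test, with n the control group:

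n = (1 + 1/2) × (1.960 + 0.842)² / 0.5² = 1.5 × 7.849 / 0.25 = 47.1, rounded up to 48.

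This gives 48 + 96 = 144, as stated. Power at 96 v 48 is 0.802 by noncentral t and 0.807 by the normal approximation. A one-sided test gives 114 and does not reproduce the figure. The planned 80% therefore comes from an unadjusted comparison within one diagnosis and never relied on a stratum term.

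**2. Bias from pooling.** Each diagnosis is planned at 120 v 60. In the pooled 240 v 120 comparison both groups are half depression and half anxiety, so a gap between diagnoses cancels from the difference in means. There is no bias while both lists hold 2:1.

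**3. Standard error from pooling.** Set the within-diagnosis SD to 1 and let the diagnoses differ by δ in mean cost, QALYs or net benefit. The article gives no δ, so 0.3, 0.5 and 1.0 are assumptions.

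- True SE under the stratified design: √(1/240 + 1/120) = 0.1118.
- Pooled variance seen by an analysis that ignores diagnosis: 1 + δ²/4.
- Ratio of reported to true SE: √(1 + δ²/4).

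| Assumed δ (SD) | Between-diagnosis share of variance, (δ²/4)/(1 + δ²/4) | SE ratio | Too wide by |
|---|---|---|---|
| 0.3 | 2.2% | √1.0225 = 1.011 | 1% |
| 0.5 | 5.9% | √1.0625 = 1.031 | 3% |
| 1.0 | 20% | √1.25 = 1.118 | 12% |

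A simulation of the 240 v 120 comparison (100,000 runs per row) gave ratios of 1.011, 1.031 and 1.119, in agreement with the formula. With no gap the ratio is 1. Equal arms are the worst case: for a share p in one diagnosis the added variance is p(1 − p)δ², which is largest at p = 1/2.

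**4. Effect on the CEAC.** On a normal approximation, the height of the curve at a given threshold is Φ(z), with z the mean incremental net benefit divided by its SE. Ignoring diagnosis divides z by 1.011, 1.031 or 1.118, so the curve is pulled towards one half at every threshold. The ICER point estimate does not change systematically.

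**The case against.** **Silence is not exclusion.** A journal article condenses the plan. Incremental means can come from an adjusted regression, the printed formula only defines an ICER, and no resampling scheme is given. This stands in part: the article does not say that the analysis is unadjusted. But the whole-group estimator is described in some detail, and as described it compares two trial groups without regard to diagnosis.

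**The effect is small and conservative.** This stands. It is about 3% at a 0.5 SD gap, and 12% needs a 1.0 SD gap that nothing in the article supports. Diagnosis-specific economic results are planned as well.

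**Stronger readings that a reader might infer, and that the article does not support.**

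- *The PHQ-9 and GAD-7 models ignore the strata.* Covariates for these models are unstated, which is ordinary in an article. If diagnosis is the stratum and the models are run within diagnosis, as the sizing suggests, they already respect it. The effect of any other factor cannot be computed, because none is named.
- *Planned power is lost.* The 144 per diagnosis reaches 80% with no stratum term. If a further balanced factor existed and explained 5% or 10% of the variance, unadjusted power at 96 v 48 would be 0.814 or 0.820, against 0.827 or 0.846 adjusted. That is 1.3 or 2.6 points forgone, from a level still above plan.
- *Type I error or power is affected in the economic analysis.* No significance test is planned for the ICER or CEAC, so only the width of the uncertainty is at issue.

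**Conclusion.** The point holds for the whole-group economic analysis. Randomisation takes place within diagnosis, but the pooled cost and QALY comparison and its bootstrap are described without diagnosis. The consequence is imprecision that is overstated, not bias: a standard error about 1%, 3% or 12% too wide for an assumed gap of 0.3, 0.5 or 1.0 SD, and a CEAC that is correspondingly too flat. This could tip a borderline result towards the follow-on decision model.

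The sizes rest on three assumptions: a gap that the article does not give, equal diagnostic arms with 2:1 in each, and incremental means and a bootstrap that are unadjusted, as the text reads. If the full plan already adjusts for or resamples within diagnosis, only the wording needs attention. The sample size and the stated power per diagnosis stand.

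**What to change.** **Economic evaluation, Statistical analysis section.** State that the whole-group differences in cost and in QALYs are estimated with diagnostic arm as a covariate, and that bootstrap samples are drawn within diagnosis by randomised group. Build the ICER and CEAC from those estimates.

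**Clinical outcomes, same section.** State that the PHQ-9 and GAD-7 mixed models are run within diagnosis. If any model pools the diagnoses, or if other stratification factors were used in the allocation, include those factors as fixed effects.

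**Cost.** A few sentences of analysis text and one degree of freedom per term. Diagnostic arm is already recorded for every participant, so no new data are needed, and sample size and trial conduct do not change.
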